#### *Voucher incentive payments*

Those allocated to the intervention group will be offered financial incentives - Love2Shop vouchers - that can be redeemed in a wide array of UK shops but not used for the purchase of cigarettes or alcohol. The total amount available is £400 if women remain abstinent at each monitoring point. Women will receive incentive payments outlined below:

£50 for attending a face-to-face appointment with their NSPS adviser and setting a quit date;

£50 if quit 4 weeks after their quit date corroborated by a carbon monoxide breath test result less than 10 ppm collected by a research nurse;

£100 if quit after 12 weeks corroborated by a carbon monoxide breath test collected by a research nurse;

£200 if they self report quit for at least 2 months when contacted for primary outcome assessment by the Helpline at 34 to 38 weeks gestation. This will be corroborated by a carbon monoxide breath test result less than 10 ppm collected by a research nurse.

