### Trial participation payments

In order to minimize loss to follow-up, particularly among control participants, £25 will be given to all participants if they provide primary outcome information (and required samples to corroborate abstinence) at 34 and 38 weeks gestation.

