### Quantitative data collection

#### *Primary outcome*

*Smoking status at 34 to 38 weeks gestation, towards the end of pregnancy*. Follow-up telephone contact will be attempted by NHS Smokefree Pregnancy Study Helpline at a random date between 34 and 38 weeks gestation allocated at the time of the initial randomization. A patient record check will be made by the NHS Smokefree Pregnancy Service administrator looking for stillbirth, miscarriage or patient death the week prior to the telephone contact at 34 to 38 weeks gestation. Miscarriage or stillbirth may not preclude a woman from receiving vouchers if they are in the intervention group.

Three attempts will be made to contact participants. If no contact is possible the participants will be followed up by the research nurse either by telephone or by a home visit after a contact detail check with the participant’s General Practitioner. If participants self report as non-smokers then a research nurse will make an appointment to collect urine and saliva for cotinine estimation (as well as a breath test for carbon monoxide to trigger the incentive payment).

If successful contact is made, the participant will be asked: ‘Have you smoked in the last 8 weeks?’ If yes ‘Have you smoked more than 5 cigarettes in that time?’ Self report will be corroborated by cotinine estimation on saliva and urine. Urine (cut-off 44.7 ng/ml) or saliva (cut-off 14.2 ng/ml) cotinine will be measured by ABS laboratories limited ([contact]).

The important aspect of the primary outcome for this phase II trial is the proportion of participants successfully followed up from the intervention but particularly the control group. If acceptable levels (about 90%) of participants can be successfully followed up with a similar proportion in the intervention and control groups, then individual randomization can be accepted as a design choice for a future phase III trial that does not produce significant bias due to differential loss to follow-up between groups.

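### Similar overall follow-up of about 90% cannot show that individual randomization avoids significant bias from differential loss to follow-up

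*Protocol article*

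**What the plan says.** The article's second research question asks whether individual randomization is efficient without bias from differential follow-up of disaffected controls. The Primary outcome section answers it with a decision rule. The rule asks for a follow-up level of roughly 90% and then states a condition and its consequence: "with a similar proportion in the intervention and control groups, then individual randomization can be accepted as a design choice" in phase III. The inference drawn is that the design is one "that does not produce significant bias due to differential loss to follow-up between groups". The same section calls the proportion followed up the important aspect of the primary outcome in this phase II trial.

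The text points two ways on what counts as followed up:

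- **Contact.** The Primary outcome section uses the term for reaching women whom the Helpline missed: "If no contact is possible the participants will be followed up by the research nurse either by telephone or by a home visit". Sampling is a later step, and only for some women: "If participants self report as non-smokers then a research nurse will make an appointment to collect urine and saliva for cotinine estimation".
- **Outcome and samples.** Trial participation payments, whose stated purpose is to limit loss to follow-up, makes the payment conditional on data and samples: £"25 will be given to all participants if they provide primary outcome information", together with the samples needed to corroborate abstinence.

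The intervention arm alone has a further payment at this assessment (Voucher incentive payments): £"200 if they self report quit for at least 2 months when contacted for primary outcome assessment by the Helpline". It is released by a breath test taken at the same nurse appointment as the cotinine samples.

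**The concern.** A quit counts only if it is claimed and then corroborated, so the outcome can be lost in two places: the woman is not reached, or she claims abstinence and gives no sample. The arms have very different reasons to complete the second step. A claimed abstainer has up to £200 + £25 = £225 at stake in the incentive arm and £25 in control.

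Claimed abstainers are a small share of each arm. A large gap in sampling among them is therefore a small gap in overall follow-up, or no gap at all if contact is what is counted. Similar overall percentages also do not show that women were lost for similar reasons.

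At stake is the trial's main design conclusion. The rule could be met while differential verification inflates the apparent benefit, and that design would then be carried into phase III.

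**Working it through.** **Inputs from the article.** 600 women, 300 per arm (Figure 2 legend); follow-up about 90% (Primary outcome); usual-care quit rate 4%, continuity-corrected chi-square test, 5% level (Sample size).

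**Step 1. The plan's own figure.** Uncorrected size per arm: n = [1.96·√(2p̄(1−p̄)) + z_power·√(p1(1−p1) + p2(1−p2))]² / d². Corrected size: n/4·[1 + √(1 + 4/(n·d))]².

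- 4% v 11.4%, 90% power: 271 uncorrected, 298 corrected.
- 4% v 10.2%, 80% power: 269 uncorrected, 300 corrected.

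The stated 600 reproduces with a two-sided test, so 300 per arm and 4% are sound inputs.

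**Step 2. Missing women against quitters.** Missing per arm at 90%: 0.10 × 300 = 30. Expected control quitters: 0.04 × 300 = 12. Ratio: 30/12 = 2.5. Suppose follow-up is exactly equal at 90%, missing counts as smoking (assumption) and no intervention quitter is lost:

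| Share of the 12 control quitters among the missing | Observed control rate | Inflation of the difference |
|---|---|---|
| 25% | 9/300 = 3% | 1 point |
| 50% | 6/300 = 2% | 2 points |
| 100% | 0/300 = 0% | 4 points |

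The last row is a bound, not a forecast. With a true 4% in both arms it would appear as 12/300 v 0/300 (Fisher p = 0.0004).

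**Step 3. Precision of the follow-up comparison.** Half-width: 1.96·√(2 × 0.9 × 0.1/300) = 0.048, or 4.8 points. This exceeds the 4-point control quit rate. If similar were judged by a 5% two-sided chi-square test (assumption), a true 4-point gap would be detected with about 37% power and a 5-point gap with about 53%.

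**Step 4. Unequal sampling among abstainers.** Assumptions, none from the article: 8% true abstinence in both arms (24 women each), every woman contacted, samples given by 95% in the incentive arm and 75% in control, unverified claims counted as smoking.

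- Verified rates: 8% × 0.95 = 7.6%; 8% × 0.75 = 6.0%.
- Unsampled women: 24 × 0.05 = 1.2 v 24 × 0.25 = 6.0. The difference is 4.8 women, and 4.8/300 = 1.6 points of follow-up if samples count. It is 0 points if contact counts.
- At 4% abstinence (12 women each): verified 3.8% v 3.0%; the follow-up difference is 12 × 0.20/300 = 0.8 points, or 0.

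Exact rejection probability, summing the product of two binomial(300) probabilities over all tables with chi-square above 3.84:

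| True abstinence in both arms | Test | With the sampling gap | Both arms at the true rate |
|---|---|---|---|
| 8% | uncorrected | 12.4% | 5.1% |
| 8% | continuity-corrected | 8.9% | 3.4% |
| 4% | uncorrected | 8.3% | 5.0% |
| 4% | continuity-corrected | 5.1% | 2.9% |

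**The case against.** **The text does not say that contact is what counts.** This is correct. A reader might infer it from how the Primary outcome section uses the term, but the payment section supports a definition that includes samples. What stands is that the term is open, and two analysts could reach different decisions from the same data.

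**The text does not tolerate a gap above 4 points.** This is also correct. A reader might infer it from the 4.8-point half-width, but the rule is silent on the margin. The detection figures in step 3 matter only if similar means not significantly different. What remains is that a bare comparison of percentages is too imprecise to exclude a gap as large as the control quit rate.

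**The illustration depends on chosen inputs.** A reader might carry away a false-positive rate of 12%. That needs 8% abstinence and an uncorrected test. With the article's 4% and its continuity-corrected test the rate is 5.1%, close to nominal, though above that test's own 2.9% under the null. The direction is the same in all four cases; the size is not fixed.

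**The protocol's claim is narrow and has safeguards.** It concerns significant bias from differential loss, not all bias. The article provides contact checks with the General Practitioner, nurse calls and home visits, the £25 payment, and interviews that include women who dropped out. These should reduce loss, but they do not make an overall percentage informative about who is lost.

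**Missing-data handling belongs in the analysis plan.** Agreed, and its absence here is not the point. The acceptance rule and the inference drawn from it are both stated in the article.

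**Conclusion.** The point holds as a defect in a stated decision rule. About 90% follow-up in similar proportions does not support the conclusion that differential loss causes no significant bias.

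Three results rest on the article's figures alone: 30 missing women per arm against 12 expected control quitters, a 4.8-point half-width around the follow-up difference, and £225 v £25 at stake for a claimed abstainer. The size of any resulting bias rests on assumptions about abstinence, sampling rates and the handling of unverified claims. In the cases worked, a 20-point sampling gap moves overall follow-up by 0 to 1.6 points and raises the false-positive rate to between 5.1% and 12.4%, depending on abstinence and test.

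The calculations do not show that such bias will occur. They show that the rule as written could miss it.

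**What to change.** Revise the decision rule in the Primary outcome section as follows.

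1. Count a woman as followed up only if her primary outcome is determined: she was contacted and, if she claims abstinence, she was sampled.
2. Base the judgement on differential loss on three further results as well as the overall proportions:
   - sample provision among self-reported abstainers, by arm;
   - the 95% confidence interval for the between-arm difference in follow-up;
   - the size of the shift in the quit-rate difference when undetermined outcomes (women not contacted, or claims not sampled) are counted as smoking, as quit, and against incentives.

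The first change alone is not enough: in the illustration it would still show a gap of only 1.6 points, so sampling by arm among claimed abstainers is the essential addition. Acceptance should not depend on the efficacy conclusion surviving these bounds, because the Sample size section says that the trial is not designed to detect a specified difference. The bounds serve to show how much the estimate could move.

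The cost is one revised passage and a few extra tables from data already collected. The downside is a criterion that is harder to meet.

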#### *Secondary outcomes*

Engagement with specialist pregnancy cessation services is achieved if the participant arrives at a first face-to-face appointment with the NSPS adviser and sets a quit date.

Quit at 4 weeks after quit date will be ascertained with the question ‘Have you smoked in the last 2 weeks, even a puff?’ at routine telephone contact by the NSPS adviser. This will be corroborated by a carbon monoxide breath test collected at routine pharmacy visits to collect NRT. These data will be available from both intervention and control groups.

##### *Birth weight*

The best methods to gather these data efficiently will be examined and tested. Maternal height and weight is recorded routinely at maternity booking and will be used to help clarify birth weight differences during data analysis. Babies of smokers are on average 300 g (10%) lighter than babies born to non-smokers [25].

##### *Unintended consequences*

We do not anticipate the provision of extra finance to participants will have any adverse effects. We are not systematically documenting adverse events that happen during pregnancy. We are, however, examining unintended consequences formally using in-depth interviews with a sample of enrolled clients. Such possible unintended consequences include, for instance, taking up smoking prior to maternity booking in order to receive incentive payments by stopping afterwards.

##### *Health economics*

Economic analysis will be undertaken alongside the trial, utilizing the costs, resource use and effectiveness data generated within the trial. For example, the cost of financial incentives, NRT, service delivery, and so on, will be collected and combined with resource use data. The number of quitters at the end of the trial will be combined with the cost data to calculate the incremental cost per late pregnancy quitter. The secondary outcome measure of child birth weight is strongly related to health care costs. Birth weight will be used to determine any difference in weight and therefore health care costs between neonates of mothers in the intervention group compared to mothers allocated to the control group.

##### *Health economic assessment*

A within-trial analysis will explore the incremental cost per late pregnancy quitter, followed by a longer term analysis incorporating the cost to the NHS of any difference in birth weight due to smoking and looking at potential lifetime quality-adjusted life year (QALY) gains to the mother and child.

A health economic model we previously developed [26] (which uses a Markov design to model the lifetime likelihood and impact of cessation, expressing the long-term health benefits of quitting smoking in terms of QALYs saved and the potential long-term reduced costs to the health service of cessation) will be used. This model will be adapted to incorporate the trial information and relevant published evidence in order to capture the short and longer term costs and health gains for both mother and child of smoking cessation during pregnancy. The outcomes will be presented in terms of the incremental cost per QALY saved. The model will be analyzed probabilistically in order to characterize uncertainty in the parameters, and estimate confidence limits around the cost and effectiveness outcomes. Areas of uncertainty identified within the model will help inform decisions about the potential value of future research. This model will ascertain whether any (and what type of) data should be collected to inform a more definitive economic evaluation and contribute to the optimal design of a Phase III trial.

### Analysis

Analysis of outcomes will be by intention-to-treat, as the intervention is the offer of financial incentives to engage with cessation services and to quit smoking.

Differences by subgroup (maternity unit, deprivation score, age group, and so on) will be explored.

### Sample size

The study is not designed to be able to detect a specified difference in the primary outcome of quit rate at 34 to 38 weeks gestation. The main objective is to inform the feasibility and design of a future definitive trial. However, assuming a quit rate of 4% in the usual care arm of the study, then with 600 participants the study will have 90% power to detect an increase in quit rates to 11.4%, or 80% power to detect an increase to 10.2%, based on a continuity-corrected *χ*^2^ test at a 5% level of significance. Even if these outcome rates were achieved in this study, a Phase III study would be required to demonstrate that the intervention can be effective in other settings.

### Overview of qualitative research components

#### *Qualitative outcomes*

The qualitative research will take the form of a process evaluation designed to inform aspects of the proposed trial. It will contribute to:

· assessing the feasibility and acceptability to women and service providers of using incentives to promote cessation during pregnancy (including identification of barriers and facilitators).

· identifying any unintended consequences of participation.

· exploring responses to randomization approaches

· providing guidance on how the intervention might be modified for the Phase III randomized controlled trial.

Interviews will be conducted with small samples of (i) pregnant women and (ii) relevant professionals by researchers at Stirling University led by [name]. This work will expand on qualitative research already undertaken with clients and professionals in relation to ‘Give it up for Baby’, the incentives scheme in Tayside [19].

Qualitative interviews will be conducted with pregnant women and professionals using semi-structured topic guides developed in line with the research aims. Topics will not be explored in a prescriptive manner but as part of an open discussion. This flexible format will enable additional salient topics and insights to emerge. In broad terms, the focus for the different respondent groups will be as follows:

One-to-one interviews with pregnant women (all of whom have engaged with the service) will explore views on issues around the delivery and promotion of the cessation service, response to incentive features and randomization, and any unintended consequences. Those interviewed prior to the trial start will be asked to respond to the concept of the incentives and the trial elements in addition to routine service elements, whilst those interviewed during the trial will also be asked to respond to these elements but based on personal experience of the trial.

Focus group interviews with pregnant women (smokers/recent ex-smokers) interviewed before the trial starts will also explore views on issues around the delivery and promotion of the cessation service, response to incentive features and randomization, and any unintended consequences. Responses can incorporate personal experiences, but will largely be based on response to the concept of these issues.

Interviews with professionals will explore issues around implementation of the intervention and the trial elements, identify challenges and ways they have been overcome, and perceived response among participants.

With the participants’ consent, all interviews and focus group discussions will be recorded as digital audio files, which will then be transcribed in full for thematic analysis. Transcripts will be organized using a thematic framework based on topics specified in the topic guide and emerging themes identified through a process of familiarization with transcript texts.

#### *Sample and recruitment for the qualitative element*

Prior to the trial starting, up to 10 pregnant smokers will be recruited from amongst those already in contact with NSPS in Glasgow. Women will be informed about the study by specialist advisers on smoking in pregnancy and asked if they are interested in participating. Those interested will be provided with an information sheet and will be asked if their details can be passed to the lead qualitative researcher. Those who consent to their details being sent on will be contacted by phone to address any queries and to arrange an interview time and place. Alternatively, if they consent at the time of the initial information being provided, interviews can be conducted following their second session with the specialist advisor. Interviews will be conducted face to face and written consent obtained.

In addition, two one-off focus groups (4 to 8 respondents each) with pregnant women (incorporating smokers/recent ex-smokers) will be conducted. Women will be recruited by the researcher through ante-natal classes or other appropriate groups attended by pregnant women and again explanations will be given and consent sought to participate.

During the trial an additional 20 women will be interviewed after they have engaged with the trial. These will be different women from those interviewed prior to the trial. Pregnant smokers will be informed about this part of the study by the NHS Smokefree Pregnancy Study Helpline and asked if they are interested in participating in the interviews as part of the initial consent process. Details of those who express an interest and consent to be contacted will be passed to the research team. Points at which individuals will be interviewed will be spread across the pregnancy (that is, at around 4, 12 and 20 weeks post-set quit date). Mechanisms will be in place to ensure there are no contraindications prior to re-contacting those to be interviewed in later pregnancy (for example, any adverse pregnancy outcomes such as miscarriage). Both continued participants and those who have dropped-out will be included in the sample.

Respondents will be recruited from two hub areas in Glasgow and Clyde. All pregnant women participants will be offered £20 in recognition of their contribution to the study.

Professionals will also be interviewed as part of the qualitative study. They will be approached through appropriate organizational structures, facilitated by study co-applicants. Information sheets will be provided and consent obtained. The professional sample is intended to reflect a range of perspectives on implementation and the conduct of the trial. They will therefore include: pregnancy smoking cessation advisor(s) and manager, Clinical Research Facility nurse(s), interviews with the NHS Stop Smoking Study Helpline staff/managers, community midwives and manager, and community pharmacy facilitator(s). Professionals will be interviewed by telephone or face to face.

## Discussion

In Scotland, up to a third of pregnant women smoke throughout pregnancy. This is responsible for a third of miscarriages, still births and sudden infant deaths during the first year of life. There would be significant long-term health gains for mother and child if smokers quit during pregnancy. At present, less than 10% of pregnant smokers take up the offer of free smoking cessation services and only 3% quit during pregnancy. Modest incentive payments to engage with cessation services and/or to quit smoking may provide a substantial benefit by decreasing pregnancy health care costs and first-year health care costs. If women stay smoke-free, long-term health care costs will be substantially reduced. The results of this phase II trial will reduce the risks associated with funding a definitive phase III multicenter trial. The phase III trial will examine the costs and benefits of providing financial incentive payments for smoking cessation during pregnancy.

